### Process evaluation

We will conduct a mixed methods process evaluation following the UK Medical Research Council guidelines to describe the intervention implementation and develop the theory of how the intervention can affect health outcomes in this context [25]. The intervention and trial design has used the extensive formative and process evaluation research from the DMagic trial [18, 19]. A process evaluation officer will collect qualitative data on how the intervention is working through (1) group observations throughout the intervention and (2) semi-structured and key informant interviews and group discussions in case study communities at two time points during the intervention. We will develop our hypothesis that health literacy is improved by the intervention [19] by integrating questions on health literacy in our survey tools [26]. We will also develop our hypothesis about the intervention effect on diabetes stigma through qualitative research and four quantitative questions asked to self-reported diabetics in the individual questionnaires. Quantitative data to describe intervention implementation will be collected from monthly reports of group supervisors who will observe an average of 33 meetings per month [18].

### Economic evaluation

Cost and cost-effectiveness analyses will be conducted from both the health system and societal perspectives. Costs of implementing the intervention will be collected prospectively from the project accounts and input into a customised excel-based standardised costing tool designed for this purpose. Data on utilisation of NCD services from healthcare providers and costs of seeking care will be collected from the study participants during individual surveys. Incremental cost-effectiveness ratios (ICERs) will be evaluated in terms of the cost per case of intermediate hyperglycaemia and T2DM prevented and disability-adjusted life years (DALYs) averted. The robustness of the cost-effectiveness results will be assessed through a series of sensitivity analyses. In addition to cost-effectiveness analysis, an equity impact analysis will be conducted in order to assess whether the intervention has improved the equity of health service delivery and is improving the health status of those most in need. All costs will be estimated both from a financial and economic perspective and presented in international dollars.

### Management and oversight

The project is a collaboration between the Diabetic Association of Bangladesh and University College London. A Trial Steering Committee will be convened according to the DAMOCLES charter, including a statistician, epidemiologist, social scientist and those with expertise in both community interventions and T2DM. This group will meet at key time points in the project (e.g. protocol review, endline results review), with the aim to meet a minimum of once a year [27]. Their role will be to provide an independent, objective review of the study implementation and baseline data and to advise on any extension or modification of the trial design. There are no stopping rules as we do not expect the intervention to have adverse effects at either cluster or participant level and have not planned an interim analysis to check for harm or futility. As a low-risk trial, a separate Data Monitoring Committee is not planned. The trial sponsor is the Institute for Global Health, University College London ([name]; [name]).

We will also establish community advisory boards, which include community representatives from Alfadanga. They will provide advice on the research design, implementation and support effective communication, and support feedback of adverse community events. These advisory boards will be consulted at key time points (e.g. group establishment and dissemination) and when questions or challenges arise (e.g. community conflicts). The Project Management Group, including all co-investigators, will meet at least monthly via teleconference, to review project progress, challenges and protocol compliance.

### Dissemination

We plan to disseminate the impact, economic and process evaluation findings to an academic audience, policy-makers and study communities at the end of the project. Depending on the planned audience, we will hold meetings, workings and share reports, as appropriate. We will also publish results in open-access peer-reviewed journals.

## Discussion

We present the protocol for a stepped-wedge cluster randomised trial, measuring the impact of a PLA intervention to prevent T2DM in a rural Bangladeshi setting at scale. During the research design process, we had extended discussions around three key methodological challenges: SW-CRCT versus parallel-arm RCT, the timing of steps, and the number of sequences (i.e. ‘steps’).

### Stepped-wedge versus parallel arm cluster RCT

The purpose of the D:Clare trial is to replicate the effective PLA approach used during the previous DMagic trial at scale. The CONSORT extension for SW-CRCT requests that authors justify using this study design, given the greater risk of bias compared to a traditional cRCT [28].

A replication study is generally defined as following the same methodology within a different study population or context; therefore, a cRCT design would be a direct replication of the DMagic trial. Given the PLA approach significantly reduced both incidence and prevalence of T2DM in the DMagic trial, but with no measurable impacts on most secondary outcomes, we felt it important to rigorously evaluate any scale-up and further explore the mechanisms of impact. As Alfadanga Upazila is in the same district as the previous DMagic population and does not have any unique distinguishing features to warrant a re-evaluation of the intervention theory, it could be argued this is not really a replication. Rather, it raises the question of whether we would meet the criteria of equipoise needed to justify an RCT.

The other factor to consider was the 36-month timeline of the project. The PLA intervention takes 18 months, and after scheduling for project setup, ethical approvals, data cleaning and analysis, there would not be sufficient time to run two full intervention cycles back to back. Therefore, on balance we selected the SW approach due to equipoise concerns, and achieving the overall aim of scale-up within the time available.

### Timing of steps and data collection

As would be conventional for a SWT with cross-sectional data collection, we decided to collect data at the same time as the ‘steps’, i.e. when clusters switch to intervention, together with an endline survey. There is a theoretical basis that the time of year could influence not only the outcome assessment, i.e. fasting blood glucose and glucose tolerance, but also several secondary and explanatory variables, such as exercise and diet. As a rural population, farming practices, diet and work patterns are liable to change with the agricultural seasons. Therefore, surveys conducted during different seasons, with unequal proportions of data from intervention and control periods, could introduce bias. Such bias can potentially be removed at analysis, but the face validity of the trial would nevertheless be undermined. There are data showing seasonal variation in both fasting glucose and HbA1C amongst known T2DM [29–31]; however, we are not aware of any population data exploring this from South Asia. We therefore lack baseline knowledge on the direction of impact to comfortably adjust for this.

In addition, data collection during the rainy season and Ramadan present pragmatic challenges. Ramadan is also likely to have an important influence on diet and physical activity, with decreases in fasting blood glucose previously observed following Ramadan [32]. Therefore, we decided that data collection during these time periods would need to be avoided. A practical solution was to plan for all surveys during the same calendar period.

### Number of sequences

Given the considerations about the timing of steps and project duration, we explored designs with 2, 3 and 4 sequences and having steps at 3 months, 6 months, 9 months or 12 months after the first implementation of the intervention—all scenarios feasible within 36 months. Based on the DMagic process evaluation, we reasoned that the community meeting at month 10 in the PLA cycle is an important milestone when groups start to implement strategies and when we might realistically expect to observe changes in population-level knowledge and behaviours. We therefore projected that some impact may be measured by month 12 of the intervention, but is less likely before. We discussed conducting the community meeting earlier in the PLA cycle, but had concerns about deviating from the effective DMagic intervention, and process data suggested groups need this initial period for problem analysis and building collective consciousness. We also hypothesised that the intervention effect may be larger beyond the end of the planned 18-month delivery, than at 12-months, given longer exposure to the intervention. Setting a 12-month period before expecting measurable intervention effects, designs with three or more sequences and hence four or more data collection surveys would have meant excluding clusters from intermediate surveys (or from the primary analysis) which had more recently implemented the intervention.

We therefore opted for the two-sequence design as the most pragmatic balance, estimating an overall (average) primary intervention effect and also the intervention effect after 12 months (6 months before completion) and 24 months (6 after completion), relative to control. Our major concern is that finding no effect may be a design artefact if PLA takes the full 18 months to work or effects are not sustained. If we assume that it takes 6 months for diabetes status to change, the measured intervention effect at 24 months should reflect the complete intervention exposure at 18 months. We will therefore give emphasis to the impact at 24 months, if its seen to be larger than the impact after 12 months. We acknowledge however that our power to estimate the 24-month effect will be lower than for the primary effect. These pre-planned analyses of differential effects during the intervention period should provide important insights into the mechanisms and appropriate timeframe for intervention implementation in further scale-up.

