### Sample size

The sample size was calculated using a presumed baseline combined prevalence of intermediate hyperglycaemia and T2DM of 30%, an assumed exchangeable correlation structure across surveys for each cluster, and an estimated intra-cluster correlation of 0.07. A sample of 110 participants per cluster, per survey, will give 84% power at 95% confidence to detect a minimum of 30% relative reduction in disease prevalence to 21% or less. An additional 10% was added to the sample size to allow for non-response, resulting in a total target sample of 3960. We will, in addition, include individuals identified with intermediate hyperglycaemia in subsequent surveys. We estimate 360 individuals will be identified as having intermediate hyperglycaemia at baseline and included in the month 12 and 24 surveys. The sample size was calculated using Stata SE14.

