### Analysis

The primary analysis will be an intention-to-treat analysis, at the individual level, comparing the combined prevalence of intermediate hyperglycaemia and T2DM between intervention and control periods across all clusters. All participants sampled during intervention periods will be included in the primary analysis, regardless of their direct engagement with the groups. The analysis will be based on regression models that include fixed effects for intervention exposure, survey timing, and sociodemographic predictors, and random effects for geographical clustering and, where appropriate, individual and household clustering (e.g. if the same individual or household is randomly sampled in two surveys). Participants with missing data on the primary outcome will be excluded from the analysis, as we anticipate high levels of participation. All estimates of the intervention effects will be presented with 95% confidence intervals. Data analysis will be done blinded, and clusters will only be unmasked following the presentation of the primary results to the Trial Steering Committee.

Outcome data in the intervention condition are collected at 12 and 24 months after the intervention is first implemented (Fig. 1). The primary analysis will however estimate one effect of the intervention, which assumes the effect of the intervention is the same after 12 and 24 months. To explore this assumption, we a priori plan to report the estimated intervention effects at these two durations separately, fitting a model that includes two intervention duration indicators. Intuitively, we can see the midline data allow the intervention effect after 12 months relative to control to be estimated, and the endline data allow the effect after 24 months relative to 12 months to be estimated. Combining these two will give the effect of the intervention after 24 months relative to control. Assuming that the intervention effect is the same at 18 months, when the intervention activities are completed, and 24 months (i.e. it does not ‘tail off’ once groups no longer have a paid facilitator), then the 24-month effect can be interpreted as the ‘full’ intervention effect.

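### Emphasis on the 24-month effect depends on its being observed larger than the 12-month effect, so the emphasised estimate is selected on the data and tends to overstate benefit

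*Protocol article*

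**What the plan says.** Under Methods, Analysis, the protocol article defines the primary analysis, with durations in months: "The primary analysis will however estimate one effect of the intervention, which assumes the effect of the intervention is the same after 12 and 24". As a check on that assumption, "we a priori plan to report the estimated intervention effects at these two durations separately", from a model with two duration indicators. The midline survey gives 12 months against control and the endline gives 24 against 12 months: "Combining these two will give the effect of the intervention after 24 months relative to control". All intervention effects are to carry 95% confidence intervals.

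Under Discussion, Number of sequences, the authors explain why an effect may come late. Groups begin to act at about month 10, the cycle lasts 18 months, and glycaemic status is assumed to need 6 months to change. They worry that a null finding could be an artefact of the design. Then follows the rule: "We will therefore give emphasis to the impact at 24 months, if its seen to be larger than the impact after 12 months". The next sentence concedes that "our power to estimate the 24-month effect will be lower than for the primary effect".

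**The concern.** The rule is triggered by which point estimate turns out larger. The article attaches no margin, test or interval for the difference to it. It also works in one direction only: nothing is said about emphasis if the 24-month effect is the smaller one. A noisy estimate that is promoted only when it looks favourable is biased towards benefit. It also offers a second chance of a positive message when the primary result is null.

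The stated rationale (18 months of activity plus 6 months for status to change) is a reason to attend to the 24-month effect whatever it shows. It is not a reason to wait and see which estimate is larger. The trial is meant to inform policy on scale-up, so the size of the emphasised effect matters.

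**Working it through.** **Inputs (protocol article)**
- Design and Randomisation: 12 clusters, six per sequence; surveys at months 1, 12 and 24; exposure 0/1/1 and 0/0/1.
- Sample size: "presumed baseline combined prevalence of intermediate hyperglycaemia and T2DM of 30"%, falling to 21%; "an estimated intra-cluster correlation of 0.07"; exchangeable correlation across surveys; 110 per cluster per survey. The total of 3960 = 110 × 12 × 3, so the 110 appears to include the 10% non-response allowance, leaving 100 analysed.

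Negative values are reductions in prevalence.

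**Reproducing the stated power.** The article says the sample "will give 84% power at 95% confidence to detect a minimum of 30% relative reduction in disease prevalence to 21% or less". I used generalised least squares on cluster-survey means with fixed survey effects and a random cluster intercept. With p at the midpoint 0.255:
- p(1 − p) = 0.190
- between-cluster variance = 0.07/0.93 × 0.190 = 0.0143
- sampling variance per cluster-survey = 0.190/100 = 0.0019

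The single-effect standard error (SE) is 0.0305. Power = Φ(0.09/0.0305 − 1.96) = 83.9%, as stated. Using 110 per cell and p = 0.30 gives SE 0.0306 and power 83.7%, so the reading of 100 or 110 hardly matters.

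**Two-duration model, same inputs**
- SE at 12 months 0.0345; SE at 24 months 0.0592; correlation 0.857
- SE of the difference (24 minus 12) 0.0345
- power for a 9-point effect at 24 months alone: Φ(0.09/0.0592 − 1.96) = 33%

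**Selection bias.** Let D be the true amount by which the 24-month reduction exceeds the 12-month one. The rule fires with probability Φ(D/0.0345). The mean overstatement when it fires is k × φ(D/0.0345)/Φ(D/0.0345), where k = (Var24 − Cov)/0.0345 = (0.00350 − 0.00175)/0.0345 = 0.0507.

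| True effects, 12 / 24 months (points) | Rule fires | Overstatement when it fires |
|---|---|---|
| equal (0/0 or -9/-9) | 50% | 0.0507 × 0.399/0.5 = 4.0 points |
| -4.5 / -9 | 90% | 0.0507 × 0.171/0.904 = 1.0 point |
| 0 / -9 | 99.5% | 0.0507 × 0.0134/0.995 = 0.07 point |

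For a true -9 at both durations, the emphasised estimate averages about -13.0.

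**Error rates with no effect** (4 million draws from the joint normal distribution of the two estimators; benefit means a two-sided 95% interval wholly below zero)

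| What is counted | False benefit (nominal 2.5%) | Two-sided (nominal 5%) |
|---|---|---|
| Primary test alone | 2.5% | 5.0% |
| 24-month result, given that the rule fires | 5.0% | 5.0% |
| Headline strictly swapped: 24 months if the rule fires, otherwise primary | 3.7% | 5.0% |
| Either the primary or the emphasised 24-month result | 4.5% | 7.0% |

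**What the single-effect estimator weights.** In this design it equals about 1.47 × (12-month estimate) − 0.47 × (24-month estimate). With true effects 0/-9 its expectation is −0.47 × (−9) = +4.2 points, so it would almost never show benefit. With -4.5/-9 its expectation is 1.47 × (−4.5) + 0.47 × 9 = −2.4 points, and it shows benefit in about 12% of trials. This matters for the choice of remedy.

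**The case against.** The strongest reply is that emphasis is not replacement. The Analysis section keeps one primary effect and commits in advance to reporting both durations with intervals. A reader might infer that the plan swaps its primary endpoint, or that the trial's type I error is inflated. The article supports neither: it says nothing about declaring success on the 24-month result, the primary test stays at 5%, and even a strict headline swap leaves two-sided error at 5.0%. That part of the reply stands.

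A reader might also infer that the greater noise at 24 months makes that estimate look larger more often. It does not. With equal effects the rule fires half the time whatever the relative noise; the noise sets the size of the bias, not its frequency.

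It is also fair that the authors expected a larger late effect and gave reasons, and that if they are right the bias is small. But the primary analysis assumes equal effects, and there the bias is largest.

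Finally, the sentence is in the Discussion, and a detailed analysis plan was still to be written. That plan may settle the matter. The point here, however, is a rule the article states, not one it omits.

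**Conclusion.** The point holds for the emphasis sentence alone. The rule selects on the data in one direction, and the emphasised 24-month estimate overstates benefit by about 0 to 4 points depending on the true time course, against a 9-point target. False benefit with no true effect rises from 2.5% to between 3.7% and 5.0%, depending on what is counted. The primary test is unaffected. This should be changed, but it does not undermine the primary analysis.

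The figures assume a normal approximation without small-sample correction, the article's ICC and exchangeable correlation, and no contribution from the re-sampled participants with intermediate hyperglycaemia. If the correlation between surveys decayed (cluster autocorrelation 0.8, my assumption, with 110 per cell), the bias under equal effects would be about 5.6 points, with similar error rates.

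**What to change.** Delete the conditional clause and fix the roles in advance, whatever the estimates show:
- The primary single effect carries the confirmatory conclusion.
- The 12-month effect, the 24-month effect and their difference are always reported together, with 95% confidence intervals and the same prominence.
- Any claim that the effect grows is judged by the interval for 24 versus 12 months.

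Reporting both durations is already planned; what is new is the interval for the difference and the fixed prominence.

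Do not make the 24-month estimate conditional on a significant primary result. Because the single-effect estimator gives the 24-month effect a weight of about −0.47, such a gate would block it in the delayed-effect case that worries the authors.

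The cost is a sentence or two and no data. The freedom to lead with the larger estimate is lost. The intervals will also be wide: about ±1.96 × 5.9 = ±11.6 points at 24 months and ±1.96 × 3.45 = ±6.8 points for the difference. According to Trial status, activities were paused soon after the baseline survey began and had not resumed, so on the article's account this can be settled before any comparison of durations exists.

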## Trial status

Protocol version 1.3 (10 December 2019).

The baseline survey started on 11 February 2020, and 52 of the 108 planned PLA groups in the first step have been established. Participant recruitment is anticipated to finish in March 2022 (Fig. 3). However, due to the COVID-19 pandemic, all intervention and data collection activities were paused on 20 March 2020 and as of 22 September 2020 have not resumed.

**Fig. 3 Fig3:**
[figure not shown]
Study time frame

## Data Availability

Any data required to support the protocol can be supplied on request.

## Abbreviations

D:Clare: Diabetes: Community-led Awareness, Response and Evaluation
DMagic: Diabetes Mellitus Action through community Groups or mHealth Information for better Control
LMIC: Low- and middle-income country
NCD: Non-communicable disease
PLA: Participatory learning and action
T2DM: Type 2 diabetes mellitus
